## Abstract

**Introduction:**

Visual impairment, specifically eye movement disorders and vestibular dysfunction may have a negative influence on the functional recovery in post-stroke patients. This type of sensory dysfunction may further be associated with poor functional outcome in patients’ post-stroke.

**Methods:**

In phase 1, a cross-sectional survey (*n* = 100) will be conducted to determine the prevalence of eye movement disorders and vestibular dysfunction in patients who sustained a stroke. A cross-sectional clinical trial (*n* = 60) will be conducted during phase 2 of the study to determine the effect of the combination of vestibular rehabilitation therapy (VRT) and visual scanning exercises (VSE) (experimental group) integrated with task-specific activities compared with the effect of task-specific activities as an intervention (control group) on patients who present with eye movement impairment and central vestibular dysfunction post-stroke. An audiologist will assess (a) visual acuity (static and dynamic), (b) nystagmus, (c) saccadic eye movements, (d) smooth pursuit eye movements, (e) vestibulo-ocular reflex, and (f) saccular, utricular, and vestibular nerve function. An independent physiotherapist will assess (1) cognitive function, (2) residual oculomotor visual performance, (3) visual–perceptual system, (4) functional balance, (5) gait, (6) functional ability, (7) presence of anxiety and/or depression, and (8) level of participation in physical activity.

**Ethics and dissemination:**

Ethics approval has been obtained from the Ethics Committee of the Faculty of Health Sciences at the University of Pretoria (UP) (374/2015). The study will be submitted as fulfillment for the PhD degree at UP. Dissemination will include submission to peer-reviewed professional journals and presentation at congresses. Training of rehabilitation team members on the integration of VSE and VRT into task-specific activities in rehabilitation will be done if the outcome of the experimental group’s functional performance is clinically and statistically significantly better than the control group on the Barthel Index.

**Trial Registration:**

Pan African Clinical Trials Registry (PACTR201509001223262).

## Introduction

A recent Cochrane review of interventions for eye movement disorders in post-stroke patients concluded that “eye movement disorders may affect over 70% of stroke patients” (1). Eye movement disorders may result in (a) “difficulty maintaining the normal ocular position” (1) and (b) “difficulty moving the eyes appropriately” (ocular motility) (1). Difficulty in “maintaining the normal ocular position” may result in disconjugate eye movement (eyes do not move in the same direction and by equal amount) (1, 2); strabismus (one eye or both eyes deviate so the eyes are no longer aligned); and/or nystagmus (frequent involuntary oscillations and other random eye movements) (1). Difficulty with spontaneous and voluntary movement of the eyes appropriately during functional activities may include impairment of (i) saccadic eye movements (1) [rapid eye movements (400°–600°/s) that shifts the eyes from one target to another] (1, 2), (ii) smooth pursuit eye movements [slow movement of the eyes (1°–30°/s) that serve to keep gaze on a moving visual object of interest when the head is stationary] (3–5), (iii) fixation (ability to maintain a steady eye position on a target) (1), (iv) convergence (the ability to smoothly and automatically turn the eyes in along the midline to observe near objects with single vision) (6), (v) divergence (to turn the eyes outward for single vision of distant objects) (6), (vi) vestibulo-ocular reflex (to ensure stable images on the retina and clear vision during head movements) (1, 2, 7, 8), and (vii) palsy (inability to use the ocular muscles that move the eye horizontally or vertically) (1, 2). Ocular motility and the interpretation of the visual input gathered during eye movements are important for aligning and maintaining the body in space which is fundamental to the successful performance of functional tasks in any particular environment (9).

The anatomical location of the lesion following a hemispheric, subcortical, brainstem or cerebellar stroke may result in the following symptoms (2): (a) posterior parietal cortex [unilateral spatial neglect (USN); impaired eye movements to the contralesional hemifield], (b) posterior occipito-temporal cortical areas (visual field defect; homonymous hemianopia; abnormal eye movement into the hemianopic visual field; USN), (c) frontal lobe (saccadic eye movement and smooth pursuit eye movement dysfunction), (d) basal ganglia [impaired saccadic- and smooth pursuit eye movements; impaired convergence; USN (visual and auditory neglect)], (e) thalamus (conjugate gaze deviation contralateral to the side of the lesion; abnormal subjective visual vertical; inaccurate saccadic eye movements; USN), (f) brainstem (conjugate gaze abnormalities), and (g) cerebellum (impaired smooth pursuit eye movements and VOR suppression; gaze-holding dysfunction; ataxia of the head, trunk, and limbs) (2).

Visuomotor deficits and visual–perceptual impairments as result of eye movement disorders may affect an individual’s ability to respond to sensory input obtained from the environment and demands of the task. The inability to respond efficiently upon the sensory input from the environment and demands of the task results in a change (decrease) in postural control that leads to increased functional dependence during ADL and disability (6, 10). Clinical observations of patients with eye movement disorders following a stroke may include the following (1, 6): (1) head turn or head tilt during near (close-up) tasks, (2) avoidance of near (close-up) tasks, (3) seems to look past the observer, (4) closing or covering one eye during conversations and/or activities due to blurred vision or double-vision, (5) squinting, (6) rubs eyes a lot, (7) having difficulty maintaining eye contact, (8) neglecting one side of the body or space during functional activities, (9) bumping into walls or objects during walking or when maneuvering in a wheelchair, (10) appears to misjudge distance due to a loss of depth perception, (11) difficulty with activities of daily living due to poor eye-hand coordination – knocking objects over or missing objects during reaching, (12) “under reaching” or over reaching for objects, (13) decreased attention during conversations and/or activities (patient “day dreams”), (14) losing the place when reading, (15) having difficulty “seeing” with or without glasses, (16) letters jumping around on the page during reading, (17) experiencing eye strain or headaches, (18) portions of the page being missing when reading, (19) objects or portions of objects not being observed, (20) not seeing people or objects approaching suddenly from one side, and (21) having difficulty concentrating on tasks.

Although the association between visual impairment and impaired functional ability is recognized, “the services available to patients with visual impairment following stroke are inconsistent at present” (1). A significant proportion of patients following a stroke may present with unrecognized eye movement disorders and thus receive minimal management of their visual impairment during rehabilitation that has a wide-ranging impact on their functional performance (1, 11). The authors of the Cochrane review (1) found only two studies that investigated interventions for eye movement disorders; both of these randomized controlled trials investigated the effect of pharmacological intervention and not rehabilitation. The authors in both studies concluded that “there is insufficient evidence to reach a conclusion regarding the effectiveness of the different interventions for patients with eye movement disorders after stroke” (1). Pollock et al. (1) also considered possible management of patients with eye movement disorders that included (1) restitutive intervention that includes saccadic eye movement, smooth pursuit eye movement, and convergence training, (2) compensative intervention that consists of training of eye movements for reading, compensatory head movements, and training in ADL, and (3) standardized diagnostic assessment and management of the visual impairment following the stroke (1).

Results of a matched-pair randomized controlled trial conducted by Van Wyk et al. (12) indicated that visual scanning exercises (VSE) with saccadic eye movement training during task-specific activities for patients with USN following a stroke resulted in significant improvement on impairment and functional activity level after 4 weeks of rehabilitation. However, the authors realized that although the intervention focused on the visual system (VSE integrated with task-specific activities), the visual system also functions in intimate integration with the vestibular system and the somatosensory (proprioceptive, cutaneous, and joint receptors) systems in maintaining postural orientation and stability during functional movement.

Patients with vestibular dysfunction experience symptoms may include (1) visual blurring with head movement, (2) subjective complaints of dizziness and/or imbalance, (3) postural instability, (4) balance dysfunction, (5) increased sway in standing, (6) dysregulated gait, (7) falling, and (8) fear of falling as a result of impaired vestibulo-spinal reflexes, vestibulo-ocular reflexes (VORs), and abnormally activated vestibulo-thalamo-cortical pathways that may result in functional impairments in daily life (13–16). Various interventions that include (a) virtual reality, (b) vibrotactile feedback, (c) optokinetic stimulation, (d) VOR adaptation and saccadic exercises, and (e) gait and balance training have shown to decrease dizziness and improve postural control in patients with peripheral and central vestibular disorders (14). Although vestibular rehabilitation therapy (VRT) is indicated in patients with central and peripheral vestibular dysfunction (14), it is recommended that “enhanced engagement with physical, cognitive, and social stimulation that include novel and multi-modal stimulation result in better general functional outcomes” (13). Another recommendation is that VRT should be patient dependent and progression of the exercises should take the individual patient’s sensorimotor, cognitive, and emotional profiles into account (13, 14, 16).

Growing evidence exists that the central nervous system has the ability to compensate for vestibular impairment and re-weight sensory information (16). Although a recent Cochrane review (17) and other literature (16, 18) reported moderate to strong evidence to support VRT for persons with vestibular dysfunction, the assessment and management of central vestibular dysfunction are not integrated in standard post-stroke rehabilitation but occasionally treated as a separate problem. Limited evidence on the prevalence of (a) visual impairments specifically eye movement disorders and (b) central vestibular dysfunction in patients post-stroke has been identified in the literature. The researcher therefore identified a need to investigate the prevalence of specifically eye movement disorders and central vestibular dysfunction in the sub-acute post-stroke population. Identification of possible presence of visual impairments and central vestibular dysfunction in the post-stroke population may facilitate the development of evidence-based treatment for patients with visual impairment and central vestibular dysfunction following stroke.

There is further a lack of research evidence on the combination of VRT and VSE as part of, and integrated with task-specific activities (the gold standard in post-stroke rehabilitation), on body impairment level, functional activity, and participation levels in the treatment of post-stroke patients. The long-term effect of VSE and VRT integrated with task-specific activities on patients’ activities related to participation also needs to be investigated.

## Methods and Analysis

### Study Design

A cross-sectional survey will be conducted during phase 1 of the study to determine (1) the prevalence of visual impairments and central vestibular dysfunction in patients who are in the sub-acute phase post-stroke and (2) whether there is an association between the prevalence of visual impairments and central vestibular dysfunction in sub-acute post-stroke patients’ (a) cognitive function, (b) residual oculomotor visual performance, (c) visual–perceptual system, (d) functional balance, (e) gait, (f) functional ability, and (g) presence of anxiety and/or depression. The STrengthening the Reporting of OBservational studies in Epidemiology (STROBE) checklist will be used when reporting the results of the cross-sectional survey.

A cross-sectional clinical trial will be conducted during phase 2 of the study to determine the effect of the combination of VRT and VSE integrated with task-specific activities received by patients (Group 1) in the sub-acute phase post-stroke compared with patients who received task-specific activities alone (Group 2) on their: (a) visual impairments, (b) central vestibular dysfunction, (c) cognitive function, (d) visual–perceptual function, (e) residual oculomotor visual performance, (f) functional balance, (g) functional ability, (h) gait, and (i) level of anxiety and/or depression. The duration of the intervention period will be 2 weeks. The long-term effect of the two interventions on patients’ participation in physical activity 20 weeks after rehabilitation has been terminated will also be determined. The CONSORT statement will be used when reporting the results of the cross-sectional clinical trial.

### Research Setting

The study will be conducted at private and public rehabilitation institutions in Pretoria and Johannesburg, Gauteng, South Africa. Patients will be referred by multiple acute private and public health-care settings to the appropriate rehabilitation centers.

### Study Population

All patients who sustained a cerebral vascular incident (CVI), who are in the sub-acute phase post-stroke, and who will be admitted at one of the rehabilitation settings in Pretoria and Johannesburg, Gauteng, South Africa will be eligible to participate in the study. A CVI is defined as “the presence of a focal neurological defect due to vascular cause that is present 24 h” and results in varying degrees of dysfunction in activities of daily living (19). The sub-acute phase post-stroke is defined as the period of time since a patient is physiologically stable to 6 months post-stroke (19).

### Eligibility Criteria: Inclusion Criteria

Inclusion criteria for participants in the first phase of the trial will entail:
(a)Patients who suffered either an ischemic or hemorrhagic stroke (20) clinically diagnosed by a medical specialist (neurologist). Information on the type of stroke will be obtained from the patients’ medical records.(b)Male and female patients in the age group of 19–84 years (21).(c)Minimum Mini-Mental State Examination (MMSE) score of 7 (22).(d)Patients in the sub-acute phase following the stroke who are able to follow instructions (23) and have the capacity to provide informed consent (19).

In phase 2 of the study, patients will have in addition to these criteria also have to be diagnosed with visual impairments and/or central vestibular dysfunction.

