### Eligibility Criteria: Exclusion Criteria

Patients with the following characteristics will be excluded from the trial:
(a)Severe dementia, identified by implementing the MMSE (22).(b)History of an organic disorder or major psychiatric impairment (20).(c)Other comorbid disease or disability such as cancer or amputation that will prevent or limit assessment of the patients and their, participation or follow-up over a period of 20 weeks (20, 23).(d)Positive Dix–Hallpike test (to exclude BPPV of posterior and anterior SCCs).Because the Dix–Hallpike test and CRT (Epley) maneuver require the head rotation of 45° and the extension of 20° to 30°, patients with a history of neck surgery, recent neck trauma, severe rheumatoid arthritis, atlanto-axial and occipito-atlantal instability, cervical myelopathy or radiculopathy, carotid sinus syncope, Chiari malformation, and vascular dissection syndromes will be excluded from the study (24).(e)Positive Roll test (to exclude BPPV of horizontal SCCs).(f)Participation in other pharmacological or rehabilitation intervention studies which can confound the results of this study (20).

In phase 2 of the study, the same inclusion/exclusion criteria will be applicable as in phase 1 since patients will be randomly recruited from patients assessed in phase 1 of the study.

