#### Cross-Sectional Clinical Trial: Phase 2 of the Study

Patients with or without visual impairment and/or vestibular dysfunction will be identified based on the results of patients’ diagnosis after the battery of standardized outcome measures has been completed by two independent assessors (audiologist and physiotherapist) during phase 1 of the study. Sixty patients with (visual and/or vestibular dysfunction) identified in phase 1 of the study will be recruited to participate in the second phase of the study and randomly allocated to either Group 1 or Group 2. The study population will include the data of the first 30 patients in each group who participate in the study for all 20 weeks. The two groups of 30 patients in the respective group do not make provision for drop out of participants in the study. If patients leave the study for any reason, they will have to be replaced by another patient. The results of this first battery of tests (phase 1) will serve as the baseline measurements for phase 2 of the study. In phase 2, the researcher will determine the effect of the combination of VRT and VSE integrated with task-specific activities (*n* = 30) as an intervention approach for patients in the sub-acute phase post-stroke compared with patients who will receive task-specific activities (*n* = 30) alone as an intervention approach on their: (a) visual impairments, (b) central vestibular dysfunction, (c) cognitive function, (d) residual oculomotor visual performance, (e) visual–perceptual system, (f) functional balance, (g) ability to modify gait in response to changing task demands, (h) functional ability, and (i) presence of anxiety and/or depression after the intervention period of 2 weeks. The consecutive assessment will be repeated by the two independent assessors after the 2-week intervention period. Twenty weeks after rehabilitation has been terminated, the physiotherapist (independent assessor) will contact all patients who completed phase 2 of the study, to complete the Telephonic-Administered International Physical Activity Questionnaire (IPAQ). The aim will be to determine the effect of the combination of VRT and VSE integrated with task-specific activities for patients in Group 1 (experimental group), compared with patients who will receive task-specific activities alone Group 2 (control group) on patients’ participation activities 20 weeks after rehabilitation has been terminated.

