### Interventions

#### Experimental Group

Patients in the experimental group will receive a combination of VRT and VSE integrated with task-specific activities as part of the treatment as an “add on” intervention in this trial. A guide on the principles of VSE integrated with task-specific activities and the principles of progression of these exercises (12) is described in Table 2.

**Table 2 T2:** **Guide of the principles of saccadic eye movement training with visual scanning exercises integrated with task-specific activities and the principles of progression of these exercises (12)**.

Functional positions	Progression of task-specific activity	Visual scanning exercises integrated with task-specific activity	Progression of visual scanning exercises integrated with task-specific activity
Supine	(1) Bridging with feet on a balance mat (i.e., Airex balance mat). ↓ (2) Bridging with feet on a balance ball.	(1) Manually and/or verbally facilitate head rotation toward impaired side. ↓ (2) Perform bridging while doing saccadic eye movements by naming individual letters or numbers aloud on flash cards that are “flashed” by the physiotherapist from all directions. Example: [figure not shown] • Flash cards are shown on the impaired side by the treating physiotherapist. ↓ • Flash cards are placed against the wall on the impaired side. ↓ (3) Bridge while doing small saccadic eye movements by naming individual letters aloud on a HART-chart. Example: [figure not shown]	(1) Bridging (lift buttocks up) while naming letter aloud on flash card. Example: [figure not shown] ↓ Return to supine (drop buttocks) and immediately naming letter aloud on flash card. Example: [figure not shown] • Repeat activity with various flash cards with different letters/numbers and from different directions. ↓ (2) Bridging (lift buttocks up) while naming letter aloud on the HART-chart. Example: [figure not shown] ↓ Return to supine (drop buttocks) and immediately naming the next letter aloud on the HART-chart. [figure not shown] • Repeat activity on all lines of HART-chart. ↓ (3) Bridging (lift buttocks up) while naming letter aloud on the HART-chart from top to bottom. Example: [figure not shown] ↓ Return to supine (drop buttocks) and immediately naming the next letter aloud on the HART-chart. Example: [figure not shown] • Repeat activity on all lines of HART-chart.

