Vestibular rehabilitation therapy for treatment of central vestibular dysfunction consists of a program of exercises designed to (i) facilitate adaptation of the vestibular system, (ii) habituate the person to movement, (iii) teach sensory substitution, and (iv) as such improve a person’s balance and postural control (50).

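### The abstract describes a phase 2 population with both impairments while the criteria admit either, and patients normal on a test at baseline dilute the comparison on that test

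*Protocol article*

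**What the plan says.** The Methods paragraph of the abstract describes phase 2 as testing the combined therapy "on patients who present with eye movement impairment and central vestibular dysfunction post-stroke".

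The operative text is wider. Under Eligibility Criteria: Inclusion Criteria, phase 2 patients "also have to be diagnosed with visual impairments and/or central vestibular dysfunction". The section on phase 2 of the Data Collection Procedure agrees: "Sixty patients with (visual and/or vestibular dysfunction) identified in phase 1 of the study will be recruited". The exclusion section adds that in phase 2 "the same inclusion/exclusion criteria will be applicable as in phase 1", although the inclusion section has just added one criterion.

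Treatment is not split by impairment. Under Experimental Group, "Patients in the experimental group will receive a combination of VRT and VSE integrated with task-specific activities", and the same section describes its vestibular component this way: "Vestibular rehabilitation therapy for treatment of central vestibular dysfunction consists of a program of exercises".

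The two groups of 30 are then compared on a list that begins "a) visual impairments, (b) central vestibular dysfunction, (c) cognitive function, (d) residual oculomotor visual performance"; Study Design also opens its list with the first two of these. Table 1 assigns video nystagmography (VNG), the video head impulse test (vHIT), vestibular-evoked myogenic potentials (VEMP) and dynamic visual acuity to these objectives. Data Management and Analysis compares the groups at 2 weeks by ANCOVA adjusted for baseline, on ranks if data are skewed.

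**The concern.** Two things follow from the wording.

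First, the abstract and the criteria define different populations. A reader of the abstract would apply the result to patients with both conditions, while the trial may contain many with only one.

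Second, a patient who qualifies on eye movements alone is still counted in the vestibular comparison, and the reverse. If that patient's vestibular tests were normal at baseline, therapy can move them little. Such patients bring the average difference on that outcome closer to zero. A real effect in affected patients could then be reported as no effect on the first two objectives listed.

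**Working it through.** **Text side by side**

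| Place in the Protocol article | Population for phase 2 |
|---|---|
| Abstract, Methods | eye movement impairment *and* central vestibular dysfunction |
| Inclusion Criteria | visual impairments *and/or* central vestibular dysfunction |
| Phase 2 procedure | visual *and/or* vestibular dysfunction |

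The two operative sections agree; the abstract differs. The terms also drift: eye movement against visual, and central vestibular against vestibular.

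**The plan's own sample size**

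Inputs from Sample Size: difference δ = 0.214 and SD σ = 0.249 on the log10 Barthel scale, 30 per group, 90% power, level 0.05.

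- Standardised difference: 0.214 / 0.249 = 0.859.
- Normal approximation, two-sided: n = 2 × (1.960 + 1.282)² / 0.859² = 28.5, so 29 per group.
- t test: 29.4, so 30 per group; power at 30 is 90.5%.

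The stated 30 per group reproduces. It concerns the Barthel Index and does not depend on the impairment mix.

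**How large the dilution could be (illustration only)**

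The protocol gives no effect size or SD for any impairment test, and no split between patients with one and with both conditions. I therefore borrow δ and σ from the Barthel calculation. Assumptions: a share q has the impairment that the test measures, the effect is δ in them and zero in the others, and mean change in controls is zero.

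In all 60 the expected difference is qδ. Power depends on how noisy the unaffected patients are:

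- Case A, same noise as affected patients: variance σ² + q(1−q)δ² in the experimental arm, σ² in controls.
- Case B, no change at all in unaffected patients: variance qσ² + q(1−q)δ² in the experimental arm, qσ² in controls.

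With q = 0.5, the difference is 0.5 × 0.214 = 0.107.

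- Case A: variances 0.0620 + 0.25 × 0.0458 = 0.0734 and 0.0620; mean 0.0677, SD 0.260. Standardised difference 0.107 / 0.260 = 0.41; power about 35%.
- Case B: variances 0.0310 + 0.0114 = 0.0424 and 0.0310; mean 0.0367, SD 0.192. Standardised difference 0.107 / 0.192 = 0.56; power about 57% by the t formula and 58% by simulation.
- Affected patients only: 15 per arm, standardised difference 0.859; power 62%, or 61% when the subset sizes vary by chance.

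| Share affected (assumed) | All 60, case A to case B | Affected subset |
|---|---|---|
| 75% | 66% to 78% | 80% |
| 50% | 35% to 58% | 61% to 62% |
| 33% | 18% to 39% | 43% to 44% |

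The subset has the higher power in every row. The gain is small in case B and large in case A; real tests with retest noise in unaffected patients lie between.

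**The case against.** **The abstract may only be loose.** The article often joins the two conditions with *and* when it means them collectively, for example when stating the prevalence aim. This stands. It makes the mismatch a wording correction, and correcting it does not change who is randomised. The wider rule may also be deliberate: if each condition had 70% prevalence and they were independent (an assumption), 100 × 0.7 × 0.7 = 49 of the 100 phase 1 patients would have both, too few for 60.

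**The two conditions are not cleanly separate.** The Introduction lists vestibulo-ocular reflex impairment among eye movement disorders, and Substitution Exercises makes saccadic training part of vestibular therapy. This stands. A reader might infer that patients with one condition are given a component with no target; the documents do not support that. It also makes strata by impairment profile hard to define, which is why the remedy works test by test.

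**ANCOVA already adjusts for baseline.** It does, and that also deals with chance imbalance in the baseline value of each outcome. It does not restrict the comparison to affected patients, so the dilution remains.

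**Unaffected patients could still change.** The measures are largely quantitative, so it would be too strong to say that these patients cannot improve or that the first two objectives cannot be answered. They can be answered, for a mixed population. The claim here is only little room to improve.

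**Analysis subsets may sit in a document not shown.** That is possible, and the absence of a subset rule is not itself the fault. What this article does fix is an either-or population and a comparison of the two whole groups on both impairments.

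**Conclusion.** The point holds in a limited form. The abstract contradicts the eligibility criteria and the phase 2 procedure on who is studied. Separately, the comparisons on visual impairments and on central vestibular dysfunction include patients normal on the relevant test at baseline, which biases those differences toward zero. The direction follows from the design; the amount cannot be estimated from the protocol, and the power figures rest on an assumed share and on borrowed Barthel values.

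A reader might infer that the trial as a whole is underpowered. The documents do not support that: the sample size reproduces, and both it and the roll-out decision stated in the abstract rest on the Barthel Index, which can be scored in every patient. Nor do they show that randomisation must be stratified by impairment profile.

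**What to change.** 1. Align the abstract with Inclusion Criteria and the phase 2 procedure, use the same terms in all three places, and word the conclusion for patients with either or both conditions. Cost: wording only.
2. For each impairment outcome (VNG, vHIT, VEMP, dynamic acuity), prespecify a comparison among randomised patients who were abnormal on that test at the phase 1 baseline, reported beside the ANCOVA in all 60. Membership is known before allocation, so the subset keeps the randomised comparison. Phase 1 already needs a definition of abnormal for each test to report prevalence, so no new data are required. Cost: fewer than 60 patients in these comparisons, with wider intervals.
3. Keep all 60 for the Barthel Index, balance and gait.

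Stratifying or adjusting by impairment profile is optional. With 60 patients over several centres the strata would be sparse, and a vestibulo-ocular reflex deficit fits under both headings.
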